#### Clinical events

Survival status will be recorded at discharge and each subsequent visit (28 days, 90 days and 180 days following admission). Any patient lost to follow-up before 6 months without withdrawing consent will be traced for vital status. Other SAEs will be reported as and when the doctor becomes aware of them. The details reported will include bedside observations, laboratory data, and additional clinical narrative. During the index admission, any child fulfilling criteria for a new or additional transfusion will be recorded. At all subsequent visits hospital admissions and requirement for transfusion will be solicited.

#### Haematological recovery

Haemoglobin will be recorded at 8-hour periods up to 24 hours, then daily until discharge, then at 28 days, 90 days and 180 days.

#### Safety and adverse event reporting

The symptom checklist used at each visit will explicitly prompt for symptoms relating to possible drug toxicities. Additional safety blood tests or investigations may be performed to investigate symptoms or monitor emergent laboratory test abnormalities as clinically indicated. Serious, solicited and grade 3 or 4 adverse events will be reported on the CRF. Adverse events (clinical and laboratory) will be graded according to toxicity/severity grading.

#### Adherence

Adherence to nutritional and prophylaxis drugs will be assessed in all participants at each visit by pill counts for tablets, and nurse-administered questionnaire to the child’s carer, and where appropriate to the child (at the discretion of the nurse or doctor depending on age).

#### Health economics

The trial will measure healthcare-related costs in trial participants, starting at randomisation and continuing for the duration of follow-up. Information on hospitalisations (number, reason, and duration of stay) and other healthcare resource utilisation (visits to healthcare centres, medications) will be collected by carer interview at the 28-day, 90-day and 180-day visits. The economic evaluation will be conducted from the health services perspective. Unit costs will be attached to resource use, using the best available estimates of long-run marginal opportunity cost, to obtain a cost per patient over the period of follow-up. Routinely available national unit costs will be used where possible with local estimations where necessary. There will also be a budget impact analyses of the consequences of adopting the interventions on the health sector budgets, in each of the countries of the trial.

#### Anti-infective

Changes in inflammatory markers (eg CRP) (all participants) will be measured retrospectively together with the incidence of bacterial infections, acute febrile illness and malaria at 28 days, 90 days and 180 days from carer interview, blood cultures and non-culture-based molecular diagnostics on stored samples.

### Methods of reducing bias

Protection against bias is principally provided by a completely objective primary endpoint (mortality). Any child lost to follow-up before 6 months will be traced for vital status. Cause of death (and other clinical secondary endpoints) will be adjudicated by an Endpoint Review Committee (ERC), blinded to randomised allocations. The ERC will adjudicate on causes of death and whether fatal and non-fatal SAEs were unlikely, possibly/probably or uncertainly related to each of the randomised interventions (transfusion volume, MVMM, cotrimoxazole), if the child were to be receiving them (without knowledge of actual randomisation), to protect from bias in this open trial. The randomisations to transfusion strategies and long-term support are open because of logistical constraints – it is impossible to blind transfusion or nutritional strategies since MVMM is in a sachet and iron and folate are largely provided separately as a syrup and crushable tablets or tablets alone. Whilst cotrimoxazole prophylaxis could be blinded, the intention of this pragmatic strategy trial is to also assess likely impacts of non-compliance to taking cotrimoxazole on an antibiotic prophylaxis strategy in SA.

### Sample size calculation and statistical analysis

#### Sample size

The sample size calculation is based on the following assumptions:80 % power, 2-sided alpha = 0.013 to allow for 4 comparisons (see below)SA cases are 50 % complicated (< 4 g/dl or 4–6 g/dl with prostration/respiratory distress/known sickle cell disease/haemoglobinuria) and 50 % uncomplicated (4–6 g/dl without prostration, respiratory distress, known sickle cell disease or haemoglobinuria) [12] (and [name] personal communication)Mortality (cumulative) at 48 hours and 4 weeks is 11 % and 16 % respectively in complicated SA, and 4 % and 9 % in uncomplicated SAThe cumulative rate of re-admission, SA relapse and re-transfusion at 6 months is 12.5 % in both complicated and uncomplicated SA (in addition to mortality above)For the primary comparison of transfusion versus no transfusion in uncomplicated SA at 4 weeks, the minimum clinically relevant difference is a 50 % relative reduction (R1b): for the other primary comparison of transfusion volume (20 versus 30 ml/kg) at 4 weeks (R1a and 1b), the minimum clinically relevant difference is a 30 % relative reduction. The minimum clinically relevant difference is larger for the transfusion versus no transfusion question as provision of safe blood at all will require greater resources than provision of slightly larger versus slightly smaller blood volumes. As the same relative difference translates to a far larger absolute difference at higher event rates, for the primary comparison at 6 months (R2/3) the minimum clinically relevant difference is a 5 % absolute reduction (see below for control group event rates). Then:(R1b) comparison of transfusion versus no transfusion (50 % reduction from 9 % control mortality at 4 weeks) requires 1460 uncomplicated SA cases (1:1 allocation to 30/20 ml/kg:no transfusion, 730 in no transfusion group, 365 receiving 20 ml/kg and 365 receiving 30 ml/kg transfusions)(R1a and 1b) if the overall ratio of uncomplicated:complicated SAs is 1:1 (ie 50 % of each type), then within the subgroup randomised 1:1 to 30 versus 20 ml/kg, the ratio will be 1:2 because this comparison excludes the 50 % of uncomplicated SA randomised to no transfusion. Overall mortality at 4 weeks in this group will, therefore, be 13.67 % (0.33 × 9 % + 0.67 × 16 %). The comparison of 30 versus 20 ml/kg (30 % reduction, to 9.57 %) requires 2798 SAs, 1399 per group (split 466 uncomplicated, 933 complicated)Therefore, comparing required sample sizes for R1a and R1b, to address both parts of the transfusion question (R1) we need slightly more uncomplicated SA children per group from (R1a and 1b – *n* = 466) than (R1b – *n* = 365), and therefore the total sample size is 3730 cases (933 × 2 = 1866 complicated, 466 × 4 = 1864 uncomplicated)(R2/3) the comparison of multi-vitamins versus SOC (1:1) and cotrimoxazole prophylaxis versus SOC (1:1) requires 3162 SA cases, assuming 50 % are complicated and 50 % uncomplicated, to detect a 5 % absolute reduction from average control mortality of 25 % (0.5 × 21.5 % + 0.5 × 28.5 % at 4 weeks).

Thus, a sample size of 3730 SA cases would allow the multiple comparisons above to be made. Assuming a 6 % loss to follow-up by 6 months increases this to 3954 SA cases. As the effect sizes are reasonably large on the relative scale (> 30 % reduction), inflation factors which adjust for the factorial design are close to 1. However, assumptions are more sensitive to the relative contribution of uncomplicated:complicated SA. Capping the uncomplicated SA strata at 2000 cases (ie recruiting at least 1950 complicated SA) retains at least 80 % power to detect the differences above independently of variations in the contributing proportions of complicated SA.

Randomising uncomplicated SA (R1b) 1:1:2 between 30 ml/kg:20 ml/kg:no transfusion provides greater power for the comparison of no transfusion (SOC) versus transfusion in this group because the final randomisation ratio for transfusion:no transfusion is 1:1. In contrast, a 1:1:1 randomisation in this strata would produce a 2:1 transfusion:no transfusion ratio which has lower power.

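### The 6 % loss allowance multiplies 3730 by 1.06 instead of dividing by 0.94, so 3954 covers about 5.7 % loss; the planning alpha of 0.013 for four comparisons sums to 5.2 % (minor)

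*Protocol article*

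**What the plan says.** Both figures are in the Sample size section of the protocol article. The assumptions open with 80 % power and "2-sided alpha = 0.013 to allow for 4 comparisons". Three requirements follow:

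- Transfusion versus no transfusion in uncomplicated severe anaemia: "50 % reduction from 9 % control mortality at 4 weeks) requires 1460 uncomplicated SA cases".
- 30 versus 20 ml/kg, with control mortality said to "be 13.67 % (0.33 × 9 % + 0.67 × 16" %): "30 % reduction, to 9.57 %) requires 2798 SAs, 1399 per group (split 466 uncomplicated, 933 complicated".
- The two six-month comparisons (supplementation and cotrimoxazole): "requires 3162 SA cases, assuming 50 % are complicated and 50 % uncomplicated".

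The volume comparison needs the most children, so "the total sample size is 3730 cases (933 × 2 = 1866 complicated, 466 × 4 = 1864 uncomplicated"). The section then assumes 6 % "loss to follow-up by 6 months increases this to 3954 SA cases". It does not show the inflation formula.

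**The concern.** A sample size inflated for loss should return the required number once the stated loss is removed, and 3954 less 6 % does not return 3730. A per-comparison alpha chosen to allow for four comparisons would normally be 0.05/4 = 0.0125, and 0.013 is a little larger.

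The recruitment target and the per-comparison error level are figures that later documents tend to copy, so it is worth having them follow from their own inputs. The volume comparison sets the total and was planned at 80 % power with nothing to spare, so any shortfall shows there first.

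**Working it through.** **Inputs, all from the Sample size section.** Two-sided alpha 0.013; power 80 %; rates 9 % v 4.5 %, 13.67 % v 9.57 %, and 25 % v 20 %; required total 3730; loss 6 %; final target 3954.

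**Step 1. Reproduce the stated sample sizes.** The two-proportion formula per arm, with d = p1 − p2 and p̄ the mean of the two rates, is

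n = [z(1−α/2)·√(2p̄(1−p̄)) + z(0.80)·√(p1(1−p1) + p2(1−p2))]² / d²

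with continuity correction n_c = (n/4)·[1 + √(1 + 4/(n·d))]². Here z(0.80) = 0.8416, and z(1−α/2) is 2.4838 at alpha 0.013 and 2.4977 at 0.0125.

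| Comparison | Stated total | n_c per arm at 0.013 | Total at 0.013 | n_c per arm at 0.0125 | Total at 0.0125 |
|---|---|---|---|---|---|
| Transfusion v none | 1460 | 729.8, so 730 | 1460 | 735.6, so 736 | 1472 |
| 30 v 20 ml/kg | 2798 | 1398.1, so 1399 | 2798 | 1409.5, so 1410 | 2820 |
| Six-month comparisons | 3162 | 1581.0, so 1581 | 3162 | 1593.9, so 1594 | 3188 |

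All three stated totals reproduce at 0.013 with continuity correction, and none does at 0.0125. So 0.013 was the value used in the calculation, not just a rounded display of 0.0125.

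**Step 2. What four tests at 0.013 add up to.** Bonferroni sum: 4 × 0.013 = 0.052. If the tests were independent: 1 − 0.987⁴ = 0.0510. For comparison, 4 × 0.0125 = 0.050. The excess over 5 % is 0.2 percentage points on the sum and 0.1 under independence.

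**Step 3. Reproduce the loss allowance.** 3730 × 1.06 = 3953.8, so 3954. This is the stated figure, so the inflation was a multiplication by 1.06.

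**Step 4. What a 6 % loss requires.** If N are enrolled and 6 % are lost, 0.94·N remain.

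- Required: 3730/0.94 = 3968.1, so 3969. This is 15 more than 3954 (15/3954 = 0.4 %).
- Left from 3954: 3954 × 0.94 = 3716.8, or 3717. This is 13 below 3730.
- Loss that 3954 can absorb: (3954 − 3730)/3954 = 224/3954 = 5.7 %.

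**Step 5. Effect on power for the volume comparison.** With the same continuity-corrected formula, 1399 per arm gives 80.0 % at alpha 0.013. If 6 % were missing at day 28, about 1394 per arm would remain (1399 × 3717/3730). Power would then be 79.9 % at 0.013. Without continuity correction it would be 81.5 %.

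**Step 6. The six-month comparisons.** They need 3162 and would have 3717, giving about 87 % power. The loss formula does not affect them.

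**The case against.** The arithmetic is hard to dispute, but four objections limit what can be built on it.

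*No stated error rate is contradicted.* The article gives 0.013 as a sample-size assumption and never names 5 % as an overall level. This stands. The most that can be said is that the sum is slightly above the conventional 5 %.

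*0.013 is not shown to be a decision threshold.* A reader might infer that a result with p between 0.0125 and 0.013 would be declared significant without proper control. The document does not support that. It gives no rule for declaring significance and refers the details to a full statistical analysis plan.

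*The loss and the binding comparison are on different clocks.* The 6 % is loss by six months, whereas 3730 comes from a 28-day comparison. Because 3954 absorbs 5.7 %, an actual shortfall arises only if nearly all of the 6 % is lost in the first four weeks. Clinical events and Methods of reducing bias also provide for tracing lost children for vital status. Statistical analysis specifies time-to-event methods, so a censored child still contributes follow-up. All of this stands. A reader might infer that the trial is 15 children short in practice, but the document supports only the narrower statement that 3954 does not follow from 3730 and 6 %.

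*A lower power figure is tempting.* Combining alpha 0.0125 with the full 6 % loss by day 28 gives 79.5 % for the volume comparison. That figure stacks a worst-case loss on an alpha the article did not use, and it depends on the continuity correction. It should not be printed as the trial's power.

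The objections do not rescue the inflation step: the section itself applies 6 % to 3730, and its result is not what 6 % loss requires.

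**Conclusion.** Wrong as written, and minor. On the section's own inputs, 3954 allows for about 5.7 % loss, not 6 %; the number that matches 6 % is 3969, a difference of 0.4 %. The planning alpha of 0.013 is best read as 0.0125 rounded up. It was carried into every sample size, and over four tests it sums to 5.2 %.

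The consequence for the tightest comparison is about 0.1 percentage points of power at alpha 0.013 (80.0 % to 79.9 %), and that only if the whole six-month loss occurred by day 28. The power figures assume the continuity-corrected two-proportion formula that reproduces the article's sample sizes, the stated event rates, and lost children contributing nothing. Reading 0.013 as a rounded 0.0125 assumes an intended overall level of 5 %, which the article does not state.

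Nothing here shows an underpowered trial or an uncontrolled error rate, and no design conclusion changes.

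**What to change.** 1. Restate the loss allowance: enrolling 3954 leaves 3730 if about 5.7 % are lost. If a power figure is wanted for 6 %, give about 79.9 % for the volume comparison at alpha 0.013, and label it a worst case because the 6 % refers to six months and lost children are traced.
2. If 5 % overall control is intended, write the per-comparison level as 0.0125 and say that the sample sizes were computed at 0.013, so that they can still be reproduced. At 3730 this change alone costs the volume comparison about 0.4 percentage points of power. If 5 % overall control is not intended, state what overall level is.

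The cost is a few words in one section. Enrolment need not rise, and the multiplicity method need not change. A step-down procedure such as Holm's would be a preference here, not a correction.

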### Statistical analysis

The analyses will be described in detail in a full Statistical Analysis Plan. In brief, each intervention is hypothesised to be superior to SOC and, therefore, the proposed analysis is intention-to-treat, including all randomised patients. The primary analysis will compare: a) transfusion versus no transfusion (strata b only) and b) 20 ml/kg versus 30 ml/kg (strata a and b) in terms of the proportion of children with fatal outcome 28 days after randomisation. Primary outcome analysis will use time-to-event methods (Kaplan-Meier, log-rank test, proportional hazards models) to the timepoints specified for primary and secondary outcomes, stratified by centre and anaemia severity at baseline. Correction of anaemia will also be analysed using time-to-event methods.

Pre-specified subgroup analyses will include each of the other randomised allocations (ie exploration of interactions in the factorial design), together with the other randomisation stratification factor (centre) and the anaemia stratification factor (a versus b) for the transfusion randomisation. We will also investigate a priori whether there was any evidence for a different impact of the interventions according to the following categorical variables: previous receipt of a transfusion (ever or at another health centre in this illness); speed (rate) at which the transfusion is administered; fever; malaria; microbiological evidence of sepsis (blood culture or retrospective molecular diagnosis); HIV; known or previously undiagnosed sickle cell disease.

For the cotrimoxazole prophylaxis and MVMM supplementation randomisations the primary analysis will be intention-to-treat based on all randomised participants, as above. However, secondary analyses will be restricted to: (i) patients discharged alive, and (ii) patients discharged alive in whom these interventions were neither mandated nor contraindicated (ie excluding HIV-infected children and those with known GP6D deficiency from the cotrimoxazole randomisation, and excluding children admitted for severe acute malnutrition from the supplementation randomisation).

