
To operationalise the trial on a day-to-day basis the manual of operations stipulates that the clinical teams must first check with the transfusion services that blood is available and the adequacy of stocks of blood packs. If there are no supplies then at these times no screening and enrolment to the trial will occur. If, however, supplies are at a critical level, children with severe and complicated anaemia, eligible for R1a randomisation, should be screened and enrolled since they would ordinarily receive a blood transfusion [3]. However, at times when blood supplies are critically low then children with SA (Hb < 6 g/dl) without complications (and thus eligible for R1b randomisation) will not be enrolled to ensure blood is not diverted for trial use.

One final issue pertinent to the transfusion strategies is the potential for substantial variability of the haematological quality of the donor whole blood and red cell concentrates. We anticipate that this would influence haematological recovery and, therefore, have put in place measures to quality control this aspect. For each pack of blood transfused in the trial, prior to the blood being run into the gauged transfusion burette, the nurse or doctor will gently agitate the blood pack to ensure the blood is thoroughly mixed and there is no settling of red cells. Following this, the initial blood volume that will run down the administration line from the gauged burette will have an aliquot run into a sterile apex tube using an aseptic technique (to prevent contamination) for Hb and haematocrit testing of the donor blood.

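### Capping uncomplicated cases at 2000 does not protect power for transfusion versus no transfusion (R1b), because no minimum is set for the only stratum in which R1b is randomised

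*Protocol article*

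**What the plan says.** All references are to the protocol article.

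- **Sample size, assumptions:** "80 % power, 2-sided alpha = 0.013 to allow for 4 comparisons".
- **Sample size, R1b:** the target is a "50 % reduction from 9 % control mortality at 4 weeks", which "requires 1460 uncomplicated SA cases".
- **Sample size, volume comparison:** "The comparison of 30 versus 20 ml/kg (30 % reduction, to 9.57 %) requires 2798 SAs, 1399 per group". This comparison uses both strata, and it is the one that sets the total.
- **Sample size, R2/R3:** 3162 children are needed, from both strata.
- **Sample size, total:** 3730, raised to 3954 for 6% loss by 6 months.
- **Sample size, case mix:** the uncomplicated stratum is capped at 2000, which the article equates with at least 1950 complicated cases. This is said to keep at least 80% "power to detect the differences above independently of variations in the contributing proportions of complicated SA".
- **Statistical analysis:** the first primary comparison is "transfusion versus no transfusion (strata b only").
- **Discussion, blood supply:** when stocks are critically low, children with severe anaemia "without complications (and thus eligible for R1b randomisation) will not be enrolled to ensure blood is not diverted for trial use". Complicated cases are still enrolled at such times.

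**The concern.** The differences to which the power claim refers include R1b, a primary comparison. R1b draws its whole sample from the uncomplicated stratum. A cap on that stratum guards against having too few complicated children, which is the risk for the volume comparison. It does nothing against having too few uncomplicated children, which is the risk for R1b. The article sets no minimum for uncomplicated cases and no maximum for complicated ones.

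Whether to give blood at all in uncomplicated severe anaemia is one of the two transfusion questions. As written, the trial could fill all 3954 places within its stated limits and still have less than 80% power for that question. The sentence meanwhile tells those monitoring recruitment that the mix does not matter.

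**Working it through.** **Inputs (Sample size section).** Two-sided alpha 0.013 (z = 2.4838). Power 80% (z = 0.8416). R1b rates p1 = 0.09 and p2 = 0.045, so d = 0.045 and the mean rate is 0.0675. The allocation ratio is stated as: "the final randomisation ratio for transfusion:no transfusion is 1:1". Total enrolled 3954. Loss 6% by 6 months.

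**1. Reproducing the plan's figures.** Number per group before continuity correction:

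m = [z_alpha × √(2 × 0.0675 × 0.9325) + z_power × √(0.09 × 0.91 + 0.045 × 0.955)]² / d²
= [2.4838 × 0.3548 + 0.8416 × 0.3534]² / 0.045² = 686.05

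With continuity correction:

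n = (m/4) × [1 + √(1 + 4/(m × d))]² = 729.8, rounded up to 730 per group, 1460 in all.

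The same formula gives 1399 per group (2798) for 13.67% versus 9.57%, and 1581 per group (3162) for 25% versus 20%. All three match the article, so this is the plan's own method. Without the correction the totals are 1374, 2700 and 3084.

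**2. R1b power by case mix.** With U uncomplicated children enrolled, n per arm is U/2 with no loss and 0.94U/2 with 6% loss. Inverting the correction gives m = (n − 1/d)²/n, and power is

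Φ{[d√m − 2.4838 × 0.3548] / 0.3534}.

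Example: U = 1186 with 6% loss gives n = 557.4, m = 513.9 and Φ(0.393) = 65%.

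| Uncomplicated enrolled (share of 3954) | Corrected, 6% loss | Corrected, no loss | Uncorrected, 6% loss | Uncorrected, no loss |
|---|---|---|---|---|
| 1977 (50%, planned) | 90% | 92% | 92% | 93% |
| 1554 (39%) | 80% | 83% | 83% | 85% |
| 1460 (37%) | 77% | 80% | 80% | 83% |
| 1186 (30%, assumed) | 65% | 69% | 70% | 73% |
| 1000 (25%, assumed) | 55% | 59% | 61% | 64% |

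**3. Enrolment at which R1b reaches 80%.** By the plan's corrected method this is 1460 with no loss (1460/3954 = 37%) and 1460/0.94 = 1553.2, so 1554, with 6% loss (39%). Without the correction it is about 1373 to 1460 (35 to 37%).

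**4. The other comparisons.** The volume comparison has U/2 + (3954 − U) children. Its control rate is the weighted mean of 9% and 16%, with a 30% reduction. At the cap (U = 2000) that is 2954 children. Power is 82% with no loss and about 80% with 6% loss (corrected), or 84% and 81% (uncorrected). It rises as the complicated share rises. For R2/R3 the uncorrected power with 6% loss is 84% or more for any U from 0 to 2000. So the sentence holds for these comparisons, and R1b is the one left exposed.

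**5. Direction of drift.** The Discussion stops uncomplicated enrolment, and continues complicated enrolment, when blood is critically low. The Treatment strategies section has an unclear sentence on limited stocks, but its next sentence also admits uncomplicated children only when supplies are adequate. Both lower the uncomplicated share. The article gives no figure for how often this happens.

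**The case against.** **R1b has slack.** The volume comparison drives the total (466 uncomplicated children per transfusion group, against 365 for R1b). At the 1:1 mix that the article supports, R1b has 90 to 93% power. This stands. A reader might infer that R1b is, or will be, underpowered, but the documents do not support that. The share would have to fall from 50% to below roughly 35 to 39%, and nothing in the article predicts it. The 30% and 25% shares are assumptions for illustration.

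**The 6% loss is a 6-month figure.** R1b's endpoint is at 28 days, the analysis is by intention to treat with time-to-event methods, and lost children are traced for vital status. Loss by 28 days cannot exceed loss by 6 months and should be smaller. This stands too, which is why ranges from no loss to 6% loss are given. The no-loss end still leaves R1b below 80% at a 30% share.

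**The volume comparison at the cap.** A reader might also infer that the cap fails this comparison, since corrected power with 6% loss is 79.5% at 2000 uncomplicated (2954 × 0.94 = 2777 analysable, against 2798). The cap is not the cause. At the planned mix the figure is already 79.9% (3954 × 0.75 × 0.94 = 2788). That gap comes mainly from inflating by 3730 × 1.06 = 3954 instead of 3730/0.94 = 3969, a matter of rounding size. With no loss, or without the correction, power at the cap is above 80%.

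**A minimum may exist elsewhere.** This is a condensed article, and the full protocol could contain one. But the sentence credits the cap alone and claims independence from case mix, and that claim can be judged as it stands.

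**Conclusion.** The statement is wrong as written for one of the primary comparisons and right, to rounding, for the others. The sample sizes themselves reproduce exactly and need no change. For R1b, at least 80% power depends on about 1460 to 1554 uncomplicated children being enrolled by the plan's own method (37 to 39% of 3954), a condition that the cap does not secure. Below that the loss of power can be material: 65 to 73% at a 30% share and 55 to 64% at 25%.

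These figures rest on the article's event rates and alpha, a fixed total of 3954, and loss between 0 and 6%. The direction of drift follows from the article's enrolment rule; its extent is unknown. The finding is an over-broad power claim that hides a condition worth monitoring. It does not show that the trial will miss its target.

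**What to change.** 1. Limit the sentence on the cap to the volume comparison and R2/R3.
2. Add that 80% power for R1b also requires at least 1460 evaluable uncomplicated children, about 1460 to 1554 enrolled depending on loss by 28 days.
3. Have the existing Trial Steering Committee review the split between strata against that figure during recruitment.

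The cost is a corrected sentence and one line in the recruitment monitoring. The total stays at 3954 and no analysis changes. The article reports recruitment as still under way, so the split could still be watched. A fixed closure of the complicated stratum is not needed to correct the document. It would be a trade-off, since it could turn away children from the higher-mortality stratum and lengthen recruitment.
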